### Randomisation

Once the services have been recruited, randomisation will be performed using a web based randomization system which uses random permuted blocks on 1:1 allocation. Although originally we had discounted minimisation given the lack of good evidence for the impact of various variables on patient outcomes, given the variation in cluster sizes we will use the following data in our randomisation planning: team size (number of full time equivalent staff), in or out of London, number of service users registered per team. We have calculated the ratio of staff:patient in and out of London teams and in order to account for the variation we will stratify the teams by a binary factor to indicate whether a team is below or above a median ratio. Randomisation will take place after the participants have been screened for eligibility and consented to the trial. Baseline data collection will follow.

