### Sample size

The primary outcome is the total Aberrant Behaviour Checklist (ABC) score measured repeatedly at six and 12 months following recruitment. The pilot study [15] generated mean baseline ABC scores of 45.4 (SD 26.4). A reduction of 0.45 of a standard deviation on the ABC score in the ABC group compared to the TAU group is considered to be clinically important. Using an analysis of covariance approach based on a correlation of 0.48 between the baseline and post-intervention ABC measurements (as per pilot study, 15) 80 patients per arm will be required to detect a difference of 0.45 SD with 90% power and 5% significance level. Inflating for clustering within the community intellectual disability services, using the formula proposed by Eldridge et al. [31] which accounts for variable cluster sizes and an intracluster correlation of 0.062 (estimated from the pilot study), an average cluster size of 12 (we expect it to be 13, however, allowing for 10% attrition and rounding it up to the nearest integer we have used a cluster size of 12 in our calculations), and a standard deviation for the cluster size of 3, a total of 276 patients will be required. However, this sample size can be reduced as each patient will provide two measurements of ABC score. Using a correlation of 0.6 between the 6 and 12 months post intervention ABC measurements (15,16) and a cluster size of 2, a total of 442 ABC measurements from 221 patients will be required. In performing this calculation we have assumed that there will be no treatment by time period interaction over 12 months supported by the pilot studies [11,12]. To allow for 10% attrition over the 12 month period a total of 246 patients will be recruited to the trial thus requiring 19 clusters. The sample size calculation is based on the program and formulae in STATA version 12.

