### Masking

Research assistants but not teams will be blind to group allocation of the service. They will be asked to retain a diary of their estimation of which treatment the participant is allocated to and to report occasions where this has been disclosed to them in the course of their work. Unmasking will not occur until after the study endpoint and once the database is locked. Finally we will compare guesses about participant allocation between trial arms in order to determine any loss of blinding and potential bias and we will adjust for any bias detected.

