### Possible sources of bias

One potential source of bias is transfer of trained staff between trained and control teams during the trials. We have examined the turnover of health staff in a number of services which have expressed interest in participating and this is well below 13% which is considered very low based on National Health Service performance data. Furthermore contamination between study arms is unlikely given the more intensive nature of the intervention. However, PBS principles are being taught widely therefore, some knowledge of PBS will be unavoidable. We will collect information from all participating teams on the level of knowledge and training the staff may have had in delivering any aspects of PBS. Another potential source of bias may derive from variation in patient characteristics between teams. However, we do not anticipate substantial variation in this respect as the teams will cover diverse geographical areas thus reducing the possibility of bias.

Selection bias resulting from recruiting participants after cluster allocation has been revealed will be avoided by completing recruitment and screening assessment prior to randomisation.

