### Inclusion criteria

Service users: Eligible to receive care from intellectual disability services; mild to severe intellectual disability; aged 18 years and over; total ABC score of at least 15 (indicates a degree of challenging behaviour occurring at least weekly including verbal or physical aggression, hyperactivity, refusal to attend activities, non responsiveness that requires professional input).Service: Willing to participate; availability of at least two staff members willing to train; written agreement by the service manager to participate.

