#### Primary outcome measure

Changes in challenging behaviour as measured by the Aberrant Behaviour Checklist [36,37] over 12 months. The instrument has been widely used for monitoring changes in behaviour in people with intellectual disability following treatment and has demonstrated acceptable reliability and validity. The ABC scores can be separated into five different factors comprising (I) Irritability, Agitation, Crying (15 items), (II) Lethargy, Social Withdrawal (16 items), (III) Stereotypic Behaviour (7 items), (IV) Hyperactivity, Non-compliance (16 items), and (V) Inappropriate Speech (4 items). Each domain is rated on a four point scale (0–3). A total score can be obtained by adding up all domain scores. It will be completed by the person’s paid or family carer at all time points.

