### Statistical analysis

We shall follow CONSORT guidelines for the analysis of cluster randomised trials and reporting of findings (http://www.consort-statement.org/).

The baseline characteristics of the PBS and TAU groups will be summarised using means, standard deviation and proportions as appropriate. A three level regression model adjusting for baseline ABC measurements, time period and effects of clustering by services and accounting for repeated measures within subjects will be used for the primary analysis. Similar analyses will be conducted for the secondary outcomes using appropriate regression models depending on the type of outcome. Results from all secondary analyses will be presented as estimates with confidence intervals and treated as exploratory. If we encounter missing data, bias due to missing data will be investigated initially by comparing the characteristics of the trial participants with complete follow-up measurements and those who have incomplete follow-up or no outcome data, descriptively. If differences are observed in the participants’ characteristics in the descriptive analysis, factors which are likely to be associated with the outcome will be included in a multilevel logistic regression analysis (with missing yes or no as outcome) to identify predictors of missing data. If predictors associated with both missing data and the outcomes are found, these will be included in the multilevel models examining the effects of intervention on the outcomes [45]. A sensitivity analysis will also be carried out to examine the effect of PBS on ABC score after adjusting for area deprivation and the service staff to patient ratio if appropriate. Multiple imputation may be used as part of the sensitivity analysis accounting for the clustered nature of the data if considered appropriate [46-48]. As part of the sensitivity analysis we will also examine intervention by time period interaction. All analyses will be carried out on an intention to treat basis. A detailed statistical analysis plan will be agreed by the Trial Steering Committee prior to the analysis of unblinded data.

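### As written, baseline data are collected after team randomisation, so the baseline ABC covariate and baseline utility are not protected by randomisation

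*Protocol article*

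**What the plan says.** All references are to the protocol article.

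- **Order of events (Randomisation):** "Randomisation will take place after the participants have been screened for eligibility and consented to the trial. Baseline data collection will follow".
- **Who is masked (Masking):** "Research assistants but not teams will be blind to group allocation of the service".
- **Who rates the primary outcome (Primary outcome measure):** of the ABC, "It will be completed by the person’s paid or family carer at all time points".
- **How baseline is used (Statistical analysis):** "A three level regression model adjusting for baseline ABC measurements, time period and effects of clustering by services" is the core of the primary analysis. The Health economic evaluation section uses regression to control for differences in baseline utility when QALYs are compared.
- **Safeguard claimed (Possible sources of bias):** selection bias after allocation is known "will be avoided by completing recruitment and screening assessment prior to randomisation".
- **Entry criterion (Inclusion criteria):** "total ABC score of at least 15". Because screening precedes randomisation, some ABC total must exist before allocation. The article does not say whether that score is also the baseline value in the model.

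**The concern.** Adjusting for a baseline score is safe because allocation cannot have influenced it. That guarantee is lost if the score is taken after allocation and the rater may know the arm. A difference between arms in how carers score at baseline would then be treated as a pre-existing difference, and the model would correct for it when it should not.

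The safeguards in the article address other problems. Completing recruitment and screening first prevents selective enrolment but does not govern how baseline is reported. Masking the research assistants, and checking their guesses, does not mask the carer who supplies the rating. Intention-to-treat analysis does not turn a post-allocation measurement into a pre-allocation one.

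At stake are the primary effect estimate, its error rates, and the adjusted QALY difference.

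**Working it through.** **Inputs (Sample size section):** pilot baseline SD 26.4; target 0.45 SD; "correlation of 0.48 between the baseline and post-intervention ABC measurements"; 90% power; 5% significance, taken as two-sided because sidedness is not stated; ICC 0.062; mean cluster size 12 with SD 3; correlation 0.6 between 6 and 12 months; 10% attrition.

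**1. The plan's own figures reproduce, and they depend on the baseline adjustment.**

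- Without adjustment: 2 × ((1.960 + 1.282)/0.45)² = 103.8, so 104 per arm.
- With adjustment: 103.8 × (1 − 0.48²) = 79.9, so 80 per arm, as stated.
- Design effect: 1 + ((0.25² + 1) × 12 − 1) × 0.062 = 1.7285; 160 × 1.7285 = 276.6 (stated: 276).
- Two measurements each: 276 × (1 + 0.6)/2 = 220.8, so 221.
- Attrition: 221/0.9 = 245.6, so 246; 246/13 = 18.9, so 19 clusters.

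**2. How a baseline shift enters the estimate.** Let knowledge of allocation change ratings in the PBS arm, relative to TAU, by s₀ at baseline and s₁ at follow-up. With equal SDs the covariate slope is 0.48, and

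bias in adjusted effect = s₁ − 0.48 × s₀.

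**3. Baseline shifts, follow-up does not (s₁ = 0).** The target is 0.45 × 26.4 = 11.88 points. The shifts are assumptions; the documents give none.

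| Assumed s₀ (points) | Size of bias (points) | Share of target |
|---|---|---|
| 2 | 0.48 × 2 = 0.96 | 8% |
| 5 | 0.48 × 5 = 2.40 | 20% |
| 8 | 0.48 × 8 = 3.84 | 32% |

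Over-reporting at baseline in the PBS arm favours PBS; under-reporting counts against it. A simulation with 246 participants, no true effect and no clustering gave mean estimates of −0.047, −0.099 and −0.146 SD for shifts of 0.1, 0.2 and 0.3 SD. The formula gives −0.048, −0.096 and −0.144.

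**4. Effect on error rates.** The planned precision implies SE = 0.45/(1.960 + 1.282) = 0.139 SD. With b = 0.48 × shift, type I error is P(|Z + b/SE| > 1.96). Power, if the bias runs against PBS, is Φ((0.45 − b)/SE − 1.96).

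| Assumed shift | b (SD) | Type I error | Power if against PBS |
|---|---|---|---|
| 0.1 SD (2.6 points) | 0.048 | 6.4% | 82.5% |
| 0.2 SD (5.3 points) | 0.096 | 10.6% | 72.2% |
| 0.3 SD (7.9 points) | 0.144 | 17.9% | 59.6% |

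**5. The shift persists to follow-up (s₁ = s₀ = d).** Unadjusted bias is d; adjusted bias is d − 0.48d = 0.52d. For d = 5 points that is 5.0 against 2.6, so here adjustment reduces the bias.

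**6. Power under alternative covariates at the planned size.** Scaling the SE by √((1 − r²)/(1 − 0.48²)): r = 0.48 gives 90%, r = 0.4 gives 87%, r = 0.3 gives 85%, and no covariate gives 81%. The values 0.3 and 0.4 are assumptions for a screening score.

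The utility adjustment cannot be sized, because the article gives no SD or correlation for EQ-5D-Y.

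**The case against.** The strongest reply is that the covariate may already be safe. An ABC total is needed for eligibility, so a pre-randomisation score exists, and the article never says that it is not carried forward as baseline. The trial schema, which might settle this, is a figure that is not shown. This stands as a reason for moderate confidence. It does not remove the point: the Randomisation section puts baseline collection after allocation, and no section names the screening score as the covariate.

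Second, nothing says that the raters know the allocation at baseline. The unmasked people are the teams, the people trained are professionals, and the ABC is rated by carers. The article does not say when teams or carers are told. This also stands. The risk is that carers may learn the allocation, not that they are shown to know it.

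Third, the 0.48 rule is not general. It needs follow-up ratings to be unaffected; a lasting change in rating style behaves as in step 5, where adjusting helps. That stands, and the assumed shifts show sensitivity, not expected harm.

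Two stronger readings are tempting and should not be drawn:

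- A reader might infer that some baselines fall after the intervention has started, because functional assessments begin between the first two workshops. No baseline window is given, a functional assessment is not yet a behaviour plan, and the recruitment section has service users taken on for treatment after training is complete.
- A reader might infer that baseline service-use data (CSRI) are also an affected covariate. The article says when the CSRI is administered but states no adjustment for baseline cost.

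**Conclusion.** The weakness in ordering is real and should be fixed; confidence is moderate. Taken as written, the plan measures the primary covariate and the baseline utility after allocation, with unmasked teams and carers who may learn the arm. No stated safeguard covers how baseline is reported.

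The size is conditional. If baseline ratings shift differentially and follow-up ratings do not, with equal SDs and a correlation of 0.48, each point of shift moves the adjusted effect by about 0.48 points. Assumed shifts of 2 to 8 points correspond to 8% to 32% of the 11.9-point target. Direction and actual size are unknown.

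A reader might go further and conclude that the primary estimate is biased, or that the trial cannot proceed on this plan. The documents do not support that: they neither state that carers know the allocation at baseline nor exclude the screening ABC as the covariate. If the screening score is the covariate, the concern about the ABC adjustment falls away and only the utility adjustment remains.

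**What to change.** 1. **Preferred.** Complete the baseline ABC and EQ-5D-Y for all of a team's participants before that team's allocation is generated, or at least before it is released to the team and carers, and state this order. Cost: visits are re-ordered, and randomisation or release of allocation comes somewhat later.
2. **If that is not possible.** Name the pre-randomisation screening ABC total as the covariate in the primary model and treat the later ABC as descriptive. Cost: wording only, plus possibly a lower correlation with follow-up because the score is truncated at 15. Power would be about 85% to 87% if the correlation is 0.3 to 0.4, against 90% planned. Any regression to the mean from the entry threshold affects both arms alike, because the score predates allocation. This option does not protect baseline utility.
3. **At minimum, including where baselines were already taken after randomisation.** Add a sensitivity analysis of the primary outcome with the screening ABC as covariate, and record when teams and carers learned the allocation relative to the baseline assessment.

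Dropping the baseline covariate altogether is less attractive, since power at the planned size falls to about 81%. If the screening ABC is already the intended covariate, one sentence saying so settles the ABC part.

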### Masking

Research assistants but not teams will be blind to group allocation of the service. They will be asked to retain a diary of their estimation of which treatment the participant is allocated to and to report occasions where this has been disclosed to them in the course of their work. Unmasking will not occur until after the study endpoint and once the database is locked. Finally we will compare guesses about participant allocation between trial arms in order to determine any loss of blinding and potential bias and we will adjust for any bias detected.

### Possible sources of bias

One potential source of bias is transfer of trained staff between trained and control teams during the trials. We have examined the turnover of health staff in a number of services which have expressed interest in participating and this is well below 13% which is considered very low based on National Health Service performance data. Furthermore contamination between study arms is unlikely given the more intensive nature of the intervention. However, PBS principles are being taught widely therefore, some knowledge of PBS will be unavoidable. We will collect information from all participating teams on the level of knowledge and training the staff may have had in delivering any aspects of PBS. Another potential source of bias may derive from variation in patient characteristics between teams. However, we do not anticipate substantial variation in this respect as the teams will cover diverse geographical areas thus reducing the possibility of bias.

Selection bias resulting from recruiting participants after cluster allocation has been revealed will be avoided by completing recruitment and screening assessment prior to randomisation.

### Inclusion criteria

Service users: Eligible to receive care from intellectual disability services; mild to severe intellectual disability; aged 18 years and over; total ABC score of at least 15 (indicates a degree of challenging behaviour occurring at least weekly including verbal or physical aggression, hyperactivity, refusal to attend activities, non responsiveness that requires professional input).Service: Willing to participate; availability of at least two staff members willing to train; written agreement by the service manager to participate.

### Exclusion criteria

Service users: primary clinical diagnosis of personality disorder or substance misuse; relapse in pre-existing mental disorder; decision by clinical team that a referral to the study would be inappropriate, e.g. there is an open complaint investigation.Service: there are no team members willing to train; the service has already received and implements PBS for their service users.

### Interventions

#### PBS based staff training (in addition to treatment as usual)

The training, which will be supported by a treatment manual will comprise the following sections:Functional Behavioural Assessment and formulation skillsBrief Behavioural Assessment Tool for brief functional analysesb)Primary Preventionc) Secondary Prevention and Reactive Strategiesd) Periodic Service Review and Problem SolvingDeveloping individualised periodic service reviewsTrouble shooting

The training will take place on six days spread over 15 weeks. Section (a) will be delivered over a two day workshop and sections (b) to (d) over another two day workshop six weeks later. Participating proflessionals are expected to begin undertaking functional assessments of service users’ between the two workshops. The final two-day workshop eight weeks later will include discussion on how to effectively implement behavioural plans and provide problem solving strategies.

Post-workshop mentoring arrangements have been arranged.

While mentors will take all practical steps to ensure appropriate contacts are put in place, responsibility for making best use of supervision rests with participants. Throughout the training and mentoring, participants will be reminded that the present training model is aimed at intervention for individuals who do not show the most complex challenging behaviours; intervention for such individuals will require more intensive and skilled intervention. Clinical responsibility for each case and for responding to any emergencies remains with the local services. When a service user presents in a clinical emergency, the clinical team will manage the emergency following which the treatment will be resumed as appropriate.

At the end of treatment, the service users and their paid or family carers will receive a report-in accessible format for the service users- that describes the main gains from treatment and strategies to use if problems arise again.

One day training seminar on PBS will be offered to the teams allocated to the control arm at the end of the study.

#### Treatment as usual (TAU)

Most community intellectual disability services provide a range of health interventions that include but are not limited to psychiatric assessment and management, nursing support, psychology, speech and language therapy, occupational therapy and counselling. There may be some variation in resources but service users with challenging behaviour are likely to receive a range of broadly defined behavioural, psychosocial and pharmacological interventions. The latter may be influenced by or broadly based on treatment guidelines published by the British Psychological Society and the Royal College of Psychiatrists [32].

### Frequency and duration of follow up

All participants will be followed up at six and 12 months after randomisation. The flow of the study can be seen in Figure 1.

**Figure 1 Fig1:**
[figure not shown]
**Trial schema.**

### Ethical issues, research governance and consent

The study has received ethical approval by the NRES Committee London - Harrow (reference 12/LO/1378). All materials relevant to the study were made into easy read with the assistance of the service users reference group. Research and Development permissions have also been obtained for the participating teams. Details can be found in the Additional file 1: Table S1.

Written consent to contact patients and collect data for the purpose of the study will be obtained from the service users where possible, and family and paid carers. We will identify a consultee where one is available, or nominate one for those service users who lack capacity as per Mental Capacity Act 2005 [33]. Our previous work suggests that PBS is well received, of potential benefit and does no harm. As with any trial which includes TAU, participants may have a preference for the active treatment. However, it remains to be determined whether training staff in PBS is effective. Where continued participation would be inappropriate, e.g. admission to hospital under detention of the MHA 1983, participants will be withdrawn from the study. The service user’s General Practitioner will be notified of the service user’s participation in the trial. All the research team members will follow the required risk assessment procedures including guidelines for risk management and safeguarding processes.

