## Abstract

**Background:**

Many people with intellectual disability present with challenging behaviour which often has serious consequences such as the prescription of long term medication, in-patient admissions and disruption of normal daily activities. Small scale studies of Positive Behaviour Support (PBS) delivered by paid carers suggest that it reduces challenging behaviour and costs of care and improves quality of life. This study aims to investigate whether professionals training in the delivery of PBS as part of routine practice is clinically and cost effective compared to treatment as usual in community intellectual disability services.

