**Discussion:**

The study findings will have significant implications for the delivery of PBS in community based services with the potential for reducing inpatient admissions and out-of-area placements for adults with intellectual disability and challenging behaviour.

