### Health economic evaluation

Analyses will be conducted from a health services perspective and from a societal perspective. The cost-effectiveness measure will be the incremental cost per QALY gained of PBS versus treatment as usual. This will be calculated as the mean cost difference between PBS and treatment as usual divided by the mean QALY difference to give the incremental cost-effectiveness ratio (ICER). This will allow for resource allocation decisions across different health services. However, as there is no evidence of the relationship between challenging behaviour and QALYs, we will also calculate the cost per point change in the primary outcome measure, (ABC). Unit costs will be taken from standard published sources such as the Office for National Statistics and Personal Social Services Research Unit (PSSRU). The cost of PBS will also include staff resources, supervision and training. Additional information on hospital admissions and out-of-area transfers will be collected to ensure costings of the secondary care component for both trial arms are robust. Predetermined values will be used [49,50] to calculate the area under the curve using time-weighted averages of utility scores collected at baseline and each follow up point. As baseline utility scores are not controlled for prior to randomisation, utility scores may differ between trial arms at baseline. Thus, regression analysis will be used to control for differences in baseline utility scores. We will use non-parametric methods for calculating confidence intervals around the ICER based on bootstrapped estimates of the mean cost and QALY differences. The bootstrap replications will also be used to construct a cost-effectiveness [51] acceptability curve, which will show the probability that PBS is cost-effective compared to standard care at 12 months for different values of the willingness of the NHS to pay for an additional QALY. We will also subject the results to extensive deterministic (one-, two- and multi-way) sensitivity analyses.

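### Withdrawing detained participants from the study, rather than from the intervention alone, risks outcome-related loss of later ABC, quality-of-life and cost data

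*Protocol article*

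**What the plan says.** In the protocol article, Ethical issues, research governance and consent, the rule is: "Where continued participation would be inappropriate, e.g. admission to hospital under detention of the MHA 1983, participants will be withdrawn from the study". Detention is an example; the criterion itself is the open-ended one of inappropriateness.

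Four other places bear on it:

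- Frequency and duration of follow up: "All participants will be followed up at six and 12 months after randomisation".
- Statistical analysis: "All analyses will be carried out on an intention to treat basis". For missing data, the characteristics of those with and without complete follow-up are compared, then "If predictors associated with both missing data and the outcomes are found, these will be included in the multilevel models". In addition, "Multiple imputation may be used as part of the sensitivity analysis accounting for the clustered nature of the data if considered appropriate".
- Health economic evaluation: "Additional information on hospital admissions and out-of-area transfers will be collected", so that secondary care costs are sound in both arms.
- Abstract: the Background lists among the results of challenging behaviour "serious consequences such as the prescription of long term medication, in-patient admissions and disruption of normal daily activities". The Discussion describes PBS delivery in community services as "with the potential for reducing inpatient admissions and out-of-area placements".

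**The concern.** The rule removes people from the study because of something that happens after randomisation. The article itself treats in-patient admission as a consequence of challenging behaviour and fewer admissions as a possible benefit. Detention under the Mental Health Act is one kind of admission, so it is plausible that those detained are, on average, doing worse on the ABC than those who stay in.

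If their later data are not collected, three things follow. The ABC comparison at later visits is made among people filtered by an event that the intervention might influence. Utility and service-use data after the event are missing for the same people. Because the CSRI looks back over the preceding six months, a withdrawn participant's detention may fall in a period that the instrument never covers. Teams also know their allocation (Masking section), so a judgement of inappropriateness could be applied differently in the two arms. Data that were never collected cannot be recovered at the analysis stage.

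**Working it through.** **1. The texts side by side.** The follow-up section promises six- and 12-month data on everyone. The ethics section takes some participants out of the study. The economic section intends to capture admissions in both arms. The Interventions section foresees that treatment may restart once a clinical emergency has been dealt with. No section says whether withdrawal from the study also ends outcome and cost collection.

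**2. Does the missing-data plan cover it?** The primary model conditions on baseline ABC and time period and uses repeated measures, so a six-month score taken before withdrawal still counts. Adding observed predictors of missingness, or imputing from observed data, deals with missingness that observed data explain. Neither recovers a deterioration that occurred after the last assessment and led to detention.

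**3. The plan's own figures (Sample size section).**

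- Target difference: 0.45 x 26.4 = 11.9 ABC points.
- Per arm before clustering, two-sided 5% assumed: 2 x ((1.96 + 1.2816)/0.45)^2 x (1 - 0.48^2) = 79.9, so 80.
- Design effect, with CV = 3/12 = 0.25: 1 + ((0.25^2 + 1) x 12 - 1) x 0.062 = 1.7285. Total 159.7 x 1.7285 = 276.
- Two measurements with correlation 0.6: 276 x (1 + 0.6)/2 = 220.8, so 221.
- 10% attrition: 221/0.9 = 245.6, so 246. Clusters: 246/13 = 18.9, so 19.

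The stated 246 is reproduced, with 90.0% power at 221 analysed, and is not disputed. The 10% allowance protects numbers, not against bias.

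**4. Illustrative bias.** Let pT and pC be the proportions detained in the PBS and TAU arms, and D the amount in SDs by which detained participants would score above the others, taken as equal in both arms. Each full-arm mean exceeds the retained mean by p x D, so leaving these people out shifts the observed difference by (pC - pT) x D. The documents give neither p nor D, so every p and D below is an assumption. Power is at 221 analysed.

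| PBS v TAU detained | D (SD) | Shift (SD) | Shift (ABC points) | Power at the reduced effect |
|---|---|---|---|---|
| 2% v 5% | 0.5 | 0.015 | 0.015 x 26.4 = 0.4 | 88% |
| 2% v 5% | 1.5 | 0.045 | 0.045 x 26.4 = 1.2 | 83% |
| 5% v 10% | 0.5 | 0.025 | 0.025 x 26.4 = 0.7 | 87% (86.5) |
| 5% v 10% | 1.5 | 0.075 | 0.075 x 26.4 = 2.0 | 77% |
| 5% v 5% | any | 0 | 0 | 90% |

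In the first four rows the observed benefit of PBS is understated. If the rates were exchanged between arms, the shift would have the same size and would exaggerate the benefit.

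**5. How many people.** With 246/2 = 123 per arm, 5% against 2% is 6.2 against 2.5, a gap of about four participants. At 10% against 5% the gap is about six.

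**The case against.** The strongest reply is that this is one sentence in the ethics section of a condensed article. It does not say that assessments stop or that earlier data are discarded, and the full protocol may say more. The separate collection of admission data in the economic section could be read as continuing after withdrawal. That is fair: the loss of later data follows from the rule as written, but is not stated outright.

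Four stronger readings are tempting and are not supported:

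- **That the rule contradicts intention to treat.** Analysis by allocated arm is compatible with withdrawals and missing data. The rule weakens the intention-to-treat analysis; it does not logically contradict it.
- **That the worst outcomes are deleted, or that a PBS benefit is removed from the TAU arm.** Detention rates by arm and the scores of those detained are not given. Earlier scores remain usable, and the shift could be nil or go either way.
- **That all admissions trigger withdrawal.** The example is detention; other admissions are not named, and not every detention need stem from challenging behaviour.
- **That the missing cost can be priced from the article.** The £100k to £450k per annum in the background section describes individual care packages in a survey concerned with out-of-area placements. It is not the cost of detention, and it is not net of the community care that detention would replace.

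The shift formula also gives a withdrawn person no information at all. Baseline adjustment (correlation 0.48) and any six-month score (correlation 0.6) would absorb part of a raw excess, so the figures above lean high for a given D.

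What stands after all this is a stated rule that, followed literally, loses data for a reason related to outcome, with nothing shown that prevents it.

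**Conclusion.** The point holds as a weakness in a stated rule that is cheap to repair. Ending study participation on detention causes outcome-related loss of later data, is in tension with the follow-up, intention-to-treat and economic sections, and is not corrected by the planned handling of missing data.

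On the ABC the likely effect is modest: about 0.4 to 2 points of 11.9 under assumed detention of 2-5% in the PBS arm against 5-10% in the TAU arm and an assumed excess of 0.5 to 1.5 SD. It is zero with equal rates and equal excess, and of opposite sign if PBS participants are detained more often. True size and direction cannot be determined from the article. Costs of detention after withdrawal would be lost unless the admission data in the economic section go on being collected; their amount cannot be estimated from the documents.

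**What to change.** Reconcile the follow-up, ethics, statistical and economic sections by separating the end of the intervention from the end of data collection. Specifically:

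- Unless the participant or consultee withdraws consent, keep detained participants in follow-up at six and 12 months.
- Take admission and service-use data from records. Obtain the ABC from an available carer informant where feasible, and record the type of informant.
- Include these data in the intention-to-treat and economic analyses.
- Report detentions by arm.

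The cost is amendment wording and a few forms or record extractions. The ABC is specified as completed by the paid or family carer at all time points, so a change of informant is possible for a few people. Permissions were obtained for the participating teams, so collecting data elsewhere may need further permissions. This concerns data collection only; when the intervention should stop or restart is a clinical matter on which no rule is proposed.
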